### Outcomes

It is unclear if there is a clinically important improvement in the 6- to 12-month recovery period after hip and knee replacement [20]. Some evidence was found in a systematic review that clinically important improvement in the OHS and OKS occurred in the 6- to 12-month recovery period. It recommended using 12- rather than 6-month outcome data [20]. The 1-year follow-up time horizon was also discussed and accepted as appropriate by dedicated orthopaedic specialists for both THR and TKR. Thus, follow-up data for OKS, OHS and EQ-5D-3L in this study is collected 1-year post baseline (first consultation) for non-surgical patients and 1-year post-surgery for patients choosing surgery. These outcome measures and time horizon are also adopted by the steering group of The Danish Clinical Quality Program and National Clinical Registries for hip and knee OA [15].

#### Primary outcome

The primary outcome measures are OHS and OKS, depending on the indication. Both questionnaires are developed to assess pain and function for patients undergoing hip or knee replacement surgery and are available in Danish-validated versions [21, 22]. The questionnaires are short, 12-item, patient-reported outcome (PRO) questionnaires, including two domains: pain and function with six items each. The questionnaires are reported to be valid, reproducible and sensitive to clinically important changes [23]. Item scores are summed to give a total score between 0 and 48, with higher scores indicating a better outcome [23, 24].

#### Secondary outcomes

To establish if ERVIN.2 enhances clinical decision support the SDM-Q9 and SDM-Q-doc questionnaires are used, as these measure the extent to which patients are involved in decision-making from a patient perspective (SDM-Q9) and a physician perspective (SDM-Q-Doc) [25]. Both versions are applicable in preference-sensitive decisions where several treatment options exist for a particular disease [25]. The questionnaire comprises nine items and six levels. Item scores are summed to a total score between 0 and 45. The higher the score, the better the outcome [26]. SDM-Q9 is translated and validated in a Danish setting, and the validation of SDM-Q-Doc is in progress [25, 27]. SDM-Q9 and SDM-doc questionnaires are completed once immediately after the first consultation but in a separate room from the consulting surgeon. The EQ-5D-3L measures HRQoL, which is used to estimate the quality-adjusted life years (QALY), the gold standard for health economic evaluations [28]. EQ-5D-3L is available in a Danish digital version, and Danish preference weights are used to estimate utility scores [29, 30]. The questionnaire comprises five dimensions: mobility, self-care, usual activities, pain/discomfort, and anxiety/depression. Each dimension has three levels. Item scores are estimated to be a total score between ±1, where 1 equals perfect health, 0 equals dead, and negative scores equal worse than dead [31]. EQ-5D-3L data is collected concurrently with the OHS or OKS questionnaire (Table 1).

**Table 1 Tab1:** Summary of primary and secondary outcomes, questionnaire abbreviations and time for data collection

Domain for measurement	Name	Timeline for data collection
Function and pain	Oxford Hip Score (OHS)	Baseline and 1-year follow-up
Function and pain	Oxford Knee Score (OKS)	Baseline and 1-year follow-up
Health-Related Quality of Life	EQ-5D-3L	Baseline and 1-year follow-up
Shared Decision Making	SDM-Q9	Baseline
Shared Decision Making	SDM-Q-Doc	Baseline

### Participant timeline

Patients are enrolled in connection with the first consultation in the clinic and allocated directly after informed consent is given and OHS or OKS and EQ-5D-3L questionnaires are filled in. Patients who, after the first consultation, are not regarded as OA patients and have been wrongly referred to the clinic are excluded. The SDM questionnaires are filled in immediately after the consultation at baseline. Follow-up data are collected one-year post-surgery or 1-year post-consultation for surgical patients and non-surgical patients, respectively (Fig. 2).

**Fig. 2 Fig2:**
[figure not shown]
Schedule of enrolment, interventions, and assessments. *1-year post-consultation (baseline) for non-surgical patients and 1-year post-surgery for surgical patients

### Non-inferiority margin

To demonstrate non-inferiority a four points margin is used for both the OHS and OKS scales. Four points are half the size of what is considered to be a clinically relevant difference from the patient perspective [32].

### Sample size

The sample size is estimated with a 5% significance level, 90% power, 10% drop-out, and an assumed standard deviation of change equal to 10.4 points, which also corresponds to the four-point non-inferiority margin. We arrive at an estimated sample size of 130 subjects in each treatment arm. We did not account for a randomised block design in our calculation, resulting in a possibly larger sample size than necessary [30].

### Recruitment, randomisation and blinding

Trial participants are recruited through the orthopaedic outpatient clinic at Aalborg University Hospital. Patients will be randomised to either control or intervention using a randomised block design stratified by sex, age, OHS or OKS baseline scores and location of disability (hip or knee). Age (≤ 60, ≥ 61) and Oxford scores (0–40, 40–100) are subdivided into two categories. Randomisation is done using REDCap electronic data capture [33]. Block sizes are random, with possible volumes of two and four patients. Patients are randomised following baseline questionnaire completion (OHS or OKS and EQ-5D-3L) at the ePRO kiosk. The designated helper enters information on randomisation into a separate REDCap module. A randomisation key is then automatically generated, which can be extracted by the designated helper but is blinded from the patient. After randomisation, the patient receives a blue intervention group envelope or a yellow control group envelope containing the SDM-Q9 and SDM-doc questionnaires, which he or she brings to the following consultation. The randomisation key is blinded from the investigators throughout the trial and only accessible by the data monitoring committee and the treating surgeon.

Blinding of the consulting surgeon is not possible since the intervention is an interface add-on to the conventional treatment. Blinding of patients means that patients do not know that ERVIN.2 is the intervention. After trial completion, data is stored in a safe data storage with transcription logging awaiting further analysis, at which point the randomisation key is revealed to the investigators.

## Data collection and management

OHS, OKS and EQ-5D-3L data are collected through ERVIN.2, which constitutes the Case Report Form from which the data will be exported and analysed. The IT infrastructure and integrated data registers used in the it-system and ERVIN are described in Bjerregaard et al. [18]. SDM-Q9 and SDM-Doc are handed out as physical questionnaires stored in concordance with Danish legislation. Physical questionnaires are registered in Microsoft Excel by two independent persons and cross-controlled to reduce the risk of typing errors after full enrolment of patients.

The collection of follow-up data will be initiated one year from the baseline. Patients receive an OHS or OKS questionnaire and the EQ-5D-3L questionnaire electronically by secure e-mail 14, 7 and 3 days before the 1-year follow-up. Patients who do not answer on the day of 1-year follow-up will be contacted by a designated helper to fill in the questionnaires by phone.

## Statistical analysis

The primary analysis is conducted using mixed-effects linear regression with a random effect on the stratification groups. Similarly, secondary analyses are conducted using mixed-effects Poisson and linear regression for outcomes to obtain relative risks and risk differences as well as linear regression for continuous outcomes [34]. All analyses are performed in Stata 17 (StataCorp. 2021. Stata Statistical Software: Release 17. College Station, TX: StataCorp LLC).

A health economic evaluation will be conducted comparing ERVIN.2 as an add-on to the conventional consultation, following international guidelines for economic evaluations. The base-case analysis will include direct and overhead costs estimated as a mixed micro- and gross costs approach from a hospital perspective. Costs will be reported in euros (2022 index value). The measure of effect will be the gold standard for health economic evaluations, QALY, based on estimates from the EQ-5D-3L questionnaire and Danish population utility weights [30, 35]. A 1-year time horizon will be used, thus cost and effects will not be discounted. Results will be presented as an incremental cost-effectiveness ratio, plotted in an incremental cost-effectiveness (ICE)-plane to determine the cost-effectiveness of ERVIN.2 [36]. Threshold values of cost-effectiveness will only be considered if relevant, according to ICE-plane placement of the ICER. To investigate the robustness of the evaluation, relevant deterministic sensitivity analyses will be conducted based on a tornado diagram to heighten the understanding of cost and effect drivers. If necessary, additional analyses will be included, depending on the findings. In addition, probabilistic sensitivity analysis will be used to assess joint parameter uncertainty presented in an ICE scatterplot and a cost-effectiveness acceptability curve [36].

All analyses will be conducted according to intention-to-treat. However, patients who are lost to follow-up will be excluded from the base case analyses and included in sensitivity analyses, using multiple imputations and adjusting for relevant baseline differences between complete cases and patients lost to follow-up.

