### Study setting

A single-site trial will be carried out at the Department of Orthopaedic Surgery at Aalborg University Hospital, Farsoe. The department performs orthopaedic surgery on patients with OA in their hips and knees. The clinic receives 3000 new referrals for THR or TKR consultations per year, and of these, 1000 patients have joint replacement surgery. The clinic has eight permanent hip and knee specialist surgeons and a varying number of younger doctors in training programmes. The patients are referred by a general practitioner (GP) to the clinic to consult a surgeon about total hip or knee replacement following OA. Only permanent surgeons are included in the trial.

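### The primary model, as written, carries the baseline Oxford score only as a two-band stratum, so the non-inferiority interval is wider than it need be

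*Protocol article*

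**What the plan says.** Statistical analysis gives the primary model in one sentence: "The primary analysis is conducted using mixed-effects linear regression with a random effect on the stratification groups". No other model term is named for the primary outcome. The section mentions adjustment for baseline differences only for the sensitivity analyses that bring back patients lost to follow-up.

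Recruitment, randomisation and blinding shows what the strata contain: sex, age, baseline OHS or OKS, and joint. Two of these are cut from finer measurements: "Age (≤ 60, ≥ 61) and Oxford scores (0–40, 40–100) are subdivided into two categories". Four two-level factors give 2 × 2 × 2 × 2 = 16 strata. The same section gives the timing: "Patients are randomised following baseline questionnaire completion (OHS or OKS and EQ-5D-3L) at the ePRO kiosk". The full baseline score therefore exists for every randomised patient before allocation.

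Sample size works from raw change without baseline adjustment: "The sample size is estimated with a 5% significance level, 90% power, 10% drop-out", with "an assumed standard deviation of change equal to 10.4 points", a margin of four points and 130 per arm. It says that the block design was not taken into account and that the number may therefore be larger than needed. It does not say whether the 5% is one-sided or two-sided.

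**The concern.** The baseline value of the outcome is usually among the most useful covariates for a score measured again a year later. Here it is collected in full, but the stated model receives only which side of a cut-point the patient falls on. Differences between patients inside the same band stay in the residual, and chance differences between arms inside a band stay in the estimate.

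A non-inferiority conclusion rests on one confidence limit against the four-point margin, so interval width bears directly on the decision. The article also leaves open whether the 1-year score or the change is modelled. With only a banded baseline, that choice affects precision.

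**Working it through.** **Inputs from the article.** Margin 4; SD of change 10.4; 5% significance; 90% power; 10% drop-out; 130 per arm (Non-inferiority margin; Sample size). Evaluable per arm: 130 × 0.9 = 117.

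**Inputs assumed.** The correlation r between baseline and 1-year score, taken as 0.2–0.7; equal SDs at both times; normal scores; the share of patients above the cut-point, taken as 50% or 20%. The share cannot be read from the article: the bands are on a 0–100 scale and Primary outcome gives a 0–48 total, and no baseline distribution is reported.

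**Step 1: reproduce the plan's figure.**
- One-sided 5%: n = 2 × (1.645 + 1.282)² × 10.4² / 4² gives 116 per arm; 116 / 0.9 gives 129. This agrees with 130.
- One-sided 2.5%: the same formula with 1.960 gives 143, then 159. This does not agree.

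So 130 rests on one-sided 5% and unadjusted change. At 117 per arm the standard error is 10.4 × √(2/117) = 1.36. Unadjusted power is Φ(4/1.36 − 1.645) = 90.3%, or 83.7% with 1.960.

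**Step 2: how much of baseline the two bands hold.** For a cut leaving a share p on one side of a normal score, the fraction of baseline variance captured is c = φ(z_p)² / [p(1 − p)].
- p = 0.5: 0.399² / 0.25 = 0.637
- p = 0.2: 0.280² / 0.16 = 0.490

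**Step 3: residual variance with strata plus continuous baseline, divided by strata only.** The strata term is treated as absorbing all between-band variance, which favours the stated model.
- Outcome is change: (1 + r) / [2 − c(1 − r)]
- Outcome is the 1-year score: (1 − r²) / (1 − c r²)

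| r | Change: variance cut | 1-year score: variance cut |
|---|---|---|
| 0.2 | 20–25% | 1.5–2% |
| 0.5 | 11–15% | 11–15% |
| 0.7 | 6–8% | 26–33% |

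In each cell the first figure is for a 50% share and the second for a 20% share. Example at r = 0.5 and c = 0.637, for change: 1.5 / (2 − 0.3185) = 0.892, a cut of 10.8%.

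**Step 4: effect on the decision at r = 0.5.** Here 2(1 − r) = 1, so the SD of change equals the SD of the score and 10.4 serves for both outcome forms.
- Strata only: SD = 10.4 × √(1 − 0.637 × 0.25) = 9.54, or 10.4 × √(1 − 0.490 × 0.25) = 9.74.
- With continuous baseline: SD = 10.4 × √0.75 = 9.01.
- Interval width ratio: √0.892 = 0.94 to √0.855 = 0.92, so about 6–8% narrower.
- Power at 117 per arm, one-sided 5%: 93.3–94.1% rises to 96.0%.
- Power at 117 per arm, one-sided 2.5%: 88.1–89.4% rises to 92.5%.
- Number per arm for 90% power at one-sided 5% with 10% drop-out: 109–114 falls to 97, a difference of 12–17.

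**Step 5: surgeon, for scale.** With surgeons crossed with arm and an assumed intraclass correlation (ICC) of 0.01–0.05, the unadjusted requirement of 129 per arm becomes 128–123 and power goes from 90.3% to 90.5–91.5%.

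**The case against.** The strongest reply is that one sentence in a condensed article is not a full covariate list. It does not exclude other terms, and a fuller protocol or analysis plan may hold the fixed effects and the outcome form. That stands in part: a reader might infer that continuous baseline has been ruled out, and the text does not support that. But the article did choose to state the adjustment structure of its primary model, and that structure can be improved at no cost. If the adjustment already exists elsewhere, confirming it closes the point.

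It is also true that nothing here threatens validity. The strata carry a coarse baseline, randomisation keeps the estimate unbiased, and the trial was sized without any adjustment and still reaches 90% at one-sided 5%. Trial status reports 300 recruited: 300 / 2 × 0.9 = 135 evaluable per arm, with unadjusted power of about 93.5% at one-sided 5% and about 88% at one-sided 2.5%. All of this stands. It limits the point to efficiency.

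Three stronger readings should be resisted.
- **A larger gain.** Against raw change, the variance ratio (1 + r)/2 gives a cut of 35% at r = 0.3 and 25% at r = 0.5. Raw change without strata is not the model the article states, so these figures overstate what is lost.
- **The surgeon.** The article says "The clinic has eight permanent hip and knee specialist surgeons" and admits only permanent surgeons to the trial, so a reader might infer that a missing surgeon term damages the primary analysis. No ICC, caseload or rule for allotting patients to surgeons is given, and Step 5 shows a difference of only 1–6 patients per arm. Clustering matters more for SDM-Q-Doc, where the same surgeons rate many patients, but the article does not give the full terms of that model either.
- **EQ-5D and QALYs.** A reader might extend the criticism to baseline utility adjustment. An article commonly leaves that detail out, and nothing in this one supports a finding on it.

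**Conclusion.** The concern holds as a matter of precision and specification. The stated model uses the baseline Oxford score as a dichotomy when the full score is available for everyone, and the outcome form is left open. The stated 90% power is not undermined.

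The best single description of the loss is 11–15% of residual variance at r = 0.5, or an interval about 6–8% wider than it would be after adjustment. The wider range of 1.5–33% shows how far this depends on r, the outcome form and the share above the cut-point, none of which the article supplies. It also rests on equal SDs, normal scores and large-sample formulas. The gain matters most if the decision uses a two-sided 95% interval: under the r = 0.5 assumption the strata-only model then falls just short of 90% power at 117 per arm, and the adjusted model exceeds it.

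The change should be made, but the analysis as written would not be invalid without it.

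**What to change.** State the primary model in full:
- Outcome: the 1-year Oxford score.
- Fixed effects: arm; continuous baseline score of the same instrument (OHS for hips, OKS for knees); hip/knee; and a baseline-by-joint slope, because one margin and one sample size serve two instruments.
- Stratification factors: kept in the model.

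With the continuous baseline and these joint terms included, modelling change instead of the 1-year score gives the same arm estimate, so the ambiguity over outcome form no longer matters.

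If surgeon is examined, do so as a sensitivity analysis, with most interest in SDM-Q-Doc. A variance component from eight surgeons would be poorly estimated, which is a further reason not to build it into the primary model.

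The cost is wording, fixed before the randomisation key is revealed to the investigators. No new data are needed, and the sample size need not change.

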## Methods

### Trial design

A single-centre, patient-blinded 1:1 randomised-block controlled two-arm parallel-group non-inferiority trial was conducted from 30.11.2021 to 31.12.2022.

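### SDM-Q-Doc is rated by at most eight unblinded surgeons, but the stated model has no surgeon term; this costs precision and limits the result to those surgeons

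*Protocol article*

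**What the plan says.** All references are to the protocol article.

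- **Raters.** Study setting: "The clinic has eight permanent hip and knee specialist surgeons", and "Only permanent surgeons are included in the trial". Trainees are therefore not raters, and eight is a maximum; the number who actually took part is not given.
- **Instrument.** Secondary outcomes: SDM-Q-Doc gives the physician's view and SDM-Q9 the patient's. "Item scores are summed to a total score between 0 and 45". The two are the measures chosen to show whether ERVIN.2 enhances decision support.
- **Blinding and strata.** Recruitment, randomisation and blinding: the consulting surgeon cannot be blinded. The strata are sex, age, baseline Oxford score and joint. Surgeon is not among them.
- **Model.** Statistical analysis: the primary analysis is "mixed-effects linear regression with a random effect on the stratification groups". The next sentence opens with the word *Similarly*, names mixed-effects Poisson and linear regression for secondary outcomes, and ends "as well as linear regression for continuous outcomes". No surgeon effect is named for any outcome.

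**The concern.** With SDM-Q-Doc the rater is part of the measurement: a few people each produce several dozen scores. Two kinds of surgeon difference matter, and their consequences differ.

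1. Surgeons may differ in general level, some scoring high and some low whatever the arm. Leaving this in the residual adds avoidable noise.
2. Surgeons may differ in how much ERVIN.2 changes their rating. The article makes this plausible: past use of ERVIN.1 in the department is unknown, training was one-to-one, and a pilot month was added for the learning curve. The ordinary standard error does not then reflect how few surgeons the effect was observed in.

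At stake is the precision of the surgeon-rated half of the shared decision-making evidence, and how far a positive result can be carried beyond this clinic. The Discussion says that the results can guide decision-makers, which suggests wider use.

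**Working it through.** **Inputs from the article.** At most 8 surgeons; 130 patients per arm, 260 in all (Sample size); 300 recruited (Trial status); 1:1 allocation of individual patients.

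**The plan's own figure.** With margin 4, SD 10.4, one-sided 5% and 90% power, n = 2 × (1.645 + 1.282)² × 10.4² / 4² = 116 per arm. Allowing for 10% drop-out, 116 / 0.9 = 129, against the stated 130. The figure concerns the Oxford scores and is used here only for the number of ratings. No sample size is stated for SDM-Q-Doc.

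**Ratings per surgeon.** 260 / 8 = 32.5 and 300 / 8 = 37.5, if spread evenly.

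**Assumptions.** The article gives no between-surgeon variance, so a range is used. The SD of a rating within the control arm is set to 1, ICC is the share of variance due to surgeon level, and τ is the SD of the surgeon-specific arm effects in SD units. Each surgeon is taken to see patients in both arms. Individual randomisation on the day of the consultation suggests this, but the article does not say how patients reach a surgeon.

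**Case 1: level differences only (τ = 0).** The standard error without a surgeon term, relative to that with one, is 1 / √(1 − ICC):
- ICC 0.2: 1 / √0.8 = 1.12
- ICC 0.4: 1 / √0.6 = 1.29

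The test stays valid. Simulated two-sided type I error at N = 260 was 4.7% to 5.2% for ICC 0 to 0.2.

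**Case 2: the arm effect also varies by surgeon, with inference to surgeons in general.** The true variance divided by the variance that ordinary regression reports is about

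1 + (τ²/8) / [(4/N)(1 + τ²/2)].

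For N = 260 and τ = 0.2: 1 + 0.005 / (0.01538 × 1.02) = 1.32. The true error of a nominal 5% test is 2 × [1 − Φ(1.96 / √1.32)] = 8.8%.

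Simulation (10,000 trials per row, ICC 0.1, mean arm effect zero across the population of surgeons) gave these type I errors:

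| τ | No surgeon term, N = 260 | No surgeon term, N = 300 | Surgeon main effect only, N = 260 | t test on eight within-surgeon differences, N = 260 |
|---|---|---|---|---|
| 0 | 5.2% | 4.9% | 5.5% | 5.0% |
| 0.1 | 6.2% | 6.3% | 6.3% | 5.7% |
| 0.2 | 8.5% | 9.2% | 8.9% | 5.1% |
| 0.3 | 14.0% | 15.1% | 14.5% | 5.4% |
| 0.4 | 19.3% | 20.8% | 20.5% | 4.7% |

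Simulation error near 5% is about √(0.05 × 0.95 / 10,000) = 0.2 percentage points. Uneven caseloads (N = 260, no surgeon term) gave 9.9% at τ = 0.2 and 15.4% at τ = 0.3.

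A surgeon main effect recovers the precision lost in case 1 but does nothing for case 2. Only an analysis that lets the arm effect vary by surgeon holds the error near 5% for the wider inference.

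**The case against.** **This is detail for the analysis plan.** The article gives model families in two sentences, and a fuller plan may include a surgeon term. That is possible, and if so only the article's wording is affected. But the article does state a model and the one grouping it allows for, and that grouping leaves out the rater.

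**The sentence is ambiguous.** *Similarly* may carry the stratum random effect over to continuous secondary outcomes. This stands, so the article cannot be said to treat every rating as independent, or to drop the strata for SDM-Q9. Surgeon is absent on either reading.

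**The ordinary test is valid.** A reader might infer that the SDM-Q-Doc p-value is simply wrong, or that the trial has eight observations of the effect rather than 130 per arm. The article does not support that. Patients are randomised individually, and for the average effect among the participating surgeons the ordinary test is about valid. In a single-centre trial, treating those surgeons as the group of interest is legitimate. The inflated error applies only to generalising beyond them, and only if real surgeon-specific effects exist.

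**The size is assumed.** No value of τ is documented, and at 0.1 the error is only about 6%.

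**Unblinded rating is a separate matter.** If all surgeons lean towards the tool, no variance term removes that bias. The article already discloses the lack of surgeon blinding.

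**Conclusion.** The point holds in a limited form. The model stated for SDM-Q-Doc has no term for a rater who supplies about 33 to 38 of the scores.

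- The loss on any view is precision: a standard error about 12% to 29% too large if the intraclass correlation is 0.2 to 0.4, with a valid test.
- For claims about surgeons in general, the nominal 5% error is about 6% at τ = 0.1, 8.5% to 9% at 0.2 and 14% to 15% at 0.3.
- For the average effect among the participating surgeons, no material error is shown.

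These sizes rest on assumed variance components, eight surgeons, and every surgeon seeing both arms. They also assume that the consulting surgeon fills in SDM-Q-Doc. The article implies this by calling it the physician's perspective, although it also says that both questionnaires are completed in a room apart from the consulting surgeon. SDM-Q-Doc is a secondary outcome. The patient-reported primary outcome, its analysis and the sample size are not affected.

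**What to change.** 1. In the SDM-Q-Doc model, include arm, strata and a surgeon effect.
2. As a sensitivity analysis, add a surgeon-by-arm random effect with small-sample degrees of freedom, or analyse the within-surgeon arm differences (7 degrees of freedom with eight surgeons) and show them. If this does not support the main result, limit the conclusion to the participating surgeons.
3. State that the stratum effect applies to the continuous secondary outcomes, which settles the ambiguous sentence for SDM-Q9 as well.

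**Cost.** No new patients or visits. The sensitivity interval will usually be wider: the t critical value is 2.365 on 7 degrees of freedom against 1.969 on 258, a ratio of 1.20, partly offset because within-surgeon differences remove level variation. Making that analysis the main one is debatable, so it is proposed as sensitivity only. The sponsor must confirm that each form can be linked to the consulting surgeon. The article describes paper questionnaires carried in an envelope and later entered in a spreadsheet, and mentions no surgeon identifier.

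### The planned multiple imputation rests on nearly the same assumption as the complete-case analysis, so agreement between them says little about outcome- or surgery-related loss

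*Protocol article*

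**What the plan says.** The Statistical analysis section describes the primary model: "The primary analysis is conducted using mixed-effects linear regression with a random effect on the stratification groups". After stating that every analysis follows intention-to-treat, it adds that "patients who are lost to follow-up will be excluded from the base case analyses and included in sensitivity analyses", and gives the method as "using multiple imputations and adjusting for relevant baseline differences between complete cases and patients lost to follow-up". Because that statement covers every analysis, I read it as applying to the primary Oxford comparison as well as to the economic evaluation.

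Table 1 (Secondary outcomes) gives the timing of the Oxford scores and EQ-5D-3L as "Baseline and 1-year follow-up", so each has one post-baseline value. The Participant timeline fixes when that value is taken: "Follow-up data are collected one-year post-surgery or 1-year post-consultation for surgical patients and non-surgical patients, respectively". Surgery status and date are therefore needed to schedule follow-up.

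The article names no analysis that lets missing scores depart from missing at random. The tornado and probabilistic analyses belong to the economic evaluation.

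**The concern.** A missing-data sensitivity analysis is useful when it relaxes the assumption of the main analysis. Here both analyses assume that, given baseline, lost patients would have scored like the completers. With no intermediate score, imputation from baseline has only the completers' own relation of follow-up to baseline to draw on.

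This matters because ERVIN.2 is meant to change who has surgery, and operated and non-operated patients are followed on different clocks. Loss related to surgery, or to outcome itself, could differ between arms. Both analyses would then carry almost the same bias, and their agreement could be reported as robustness of a non-inferiority verdict.

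The clause also leaves open whether the baseline adjustment belongs to the imputation model or to the effect model. If it enters the effect model, the missing-data method and the adjustment set change together, and a shift from the base case cannot be attributed to missing data alone.

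**Working it through.** **Inputs from the article:** margin 4 points (Non-inferiority margin); 5% significance, 90% power, 10% drop-out, SD of change 10.4, 130 per arm (Sample size); about 1000 of 3000 yearly referrals operated, so one third (Study setting).

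**Assumed inputs:** follow-up advantage D of operated over non-operated patients of 8, 12 or 16 points; loss rates by arm and surgery; the same operated share in both arms in step 4; baseline distributions and loss mechanisms in the simulations.

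**1. The plan's own figure.** n = 2 × (1.645 + 1.282)² × 10.4² / 4² = 115.8, so 116 per arm. Then 116 / 0.9 = 128.9, so 129, against the stated 130. A one-sided 2.5% level gives 143, inflated to 159, which does not match. The 5% is therefore taken as one-sided.

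**2. Why imputation adds little.** Suppose the imputation model and the effect model share covariates. Imputed scores then scatter around the completers' fitted line, and refitting returns that line apart from simulation noise. If the covariates differ somewhat, the result is close but not identical.

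**3. Simulation (130 per arm, SD of change about 10.4, true difference 0, 20 imputations, 400 trials per scenario, strata as fixed effects).**
- Loss unrelated to outcome, or related to baseline alike in both arms: average estimates agree within about 0.02 points. Single-trial differences have an SD of 0.1 to 0.3, against about 1.4 for the estimate itself.
- Poor outcomes lost in one arm only: complete-case bias 1.06 and imputed bias 1.06 at 10% loss; 2.13 and 2.13 at 20%.
- The same mechanism with surgery status added to the imputation model (separate runs): 0.99 falls to 0.81 at 10%, and 2.06 to 1.70 at 20%.
- Exception: if loss depends on baseline in opposite directions by arm, imputation moves the stratum-adjusted estimate by about 0.2 to 0.5 points at 10% and 0.4 to 1.0 at 20%.

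**4. Surgery-related loss.** Suppose ERVIN.2 loses 2% of operated and 14% of non-operated patients. Overall loss is (1/3)(2%) + (2/3)(14%) = 10%.
- Operated share among ERVIN.2 completers: (1/3)(0.98) / 0.90 = 0.363.
- Control losing 10% of each: share 0.333. Bias = 0.030 × D, or 0.24 to 0.47 points in favour of ERVIN.2.
- Control losing 14% of operated and 8% of non-operated: share (1/3)(0.86) / 0.90 = 0.319. Bias = 0.044 × D, or 0.36 to 0.71.
- Same loss by surgery in both arms: below 0.1 in simulation.

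**5. Effect on false claims at the margin.** SE = 10.4 × √(2/117) = 1.36, with 117 = 130 × 0.9 completers per arm. For a bias of 0.2 to 0.7 favouring ERVIN.2:
- if ERVIN.2 is the tested arm: Φ(bias/1.36 − 1.645) = 6.7% to 12.9%;
- if usual care is the tested arm: Φ(−bias/1.36 − 1.645) = 3.7% to 1.5%.

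**6. Tipping shift.** Lowering imputed scores in the tested arm by δ moves the difference by (loss share) × δ. With observed difference d (tested minus reference) and the half-width unchanged, non-inferiority is lost at δ = (4 + d − 1.645 × SE) / loss share. At 10% loss, 1.645 × 1.36 = 2.24, so δ = 1.76 / 0.10 = 17.6 for d = 0 and 0.76 / 0.10 = 7.6 for d = −1.

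| Loss (130 per arm) | Criterion | d = 0 | d = −1 |
|---|---|---|---|
| 10% | one-sided 5% | 17.6 | 7.6 |
| 20% | one-sided 5% | 8.1 | 3.1 |
| 10% | two-sided 95% CI | 13.3 | 3.3 |
| 20% | two-sided 95% CI | 5.9 | 0.9 |

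Trial status reports 300 recruited. At 150 per arm (an even split assumed), 10% loss and one-sided 5%, the shifts are 19.2 and 9.2.

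**The case against.** The strongest reply is that this is a condensed article. Imputation predictors and tipping-point tables usually belong in the analysis plan, which is not shown. That stands as far as it goes. A reader might infer that surgery status is left out, or that no other missing-data analysis exists. The article supports neither reading: it lists no predictors, and it can be judged only on the check it does name. What remains is that the named check, with baseline as its only stated adjustment source, shares the base-case assumption.

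A reader might also infer that imputation simply returns the complete-case result. That is too strong. The correlation was 0.997, with a mean absolute difference of 0.08 points, when both analyses used the same continuous baseline score. It was 0.971 and 0.27 when the base case used the dichotomised score and the imputed analysis added continuous-baseline adjustment. Imputation also does useful work when baseline-related loss runs in opposite directions by arm.

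The mechanism is hypothetical. No loss rates by surgery or arm are given, and follow-up does not depend on clinic visits: patients get three e-mails and then a telephone call. This limits the likely size of the problem but does not make the check more informative.

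Finally, it is tempting to say that false claims rise from 5% to about 7–13%. That requires ERVIN.2 to be the tested arm. The abstract's Objective and the primary aim in the Background state that usual care is tested against ERVIN.2, and under that hypothesis the same bias lowers the rate to about 4–1.5%. The Background's aim of not reducing patients' health points the other way, so no single direction can be assumed.

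**Conclusion.** The point holds in a limited form. The check rests on nearly the same missing-at-random-given-baseline assumption as the complete-case analysis, so agreement between them is weak evidence about outcome- or surgery-related loss. The shared bias is about 0.2 to 0.7 points under assumed patterns that differ by arm and surgery, and below 0.1 if they are equal in both arms. With outcome-related loss in one arm it reached about 1 point at 10% loss and 2 points at 20%. All these sizes rest on assumed loss mechanisms.

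The verdict is not fragile at the planned 10% loss with an observed difference near 0. The risk lies in an estimate close to the limit, or in higher or unbalanced loss. Surgery status in the imputation model should not be read as a full cure: it removes bias that runs through surgery but only part of outcome-related bias. The shift table is therefore the essential addition.

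**What to change.** Replace the final clause of the Statistical analysis section with three rules:

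1. Impute separately by arm from the stratification factors, the continuous baseline Oxford and EQ-5D-3L scores, and surgery status with time from consultation to surgery. The surgery variables enter the imputation model only, never the effect model.
2. Fit to the imputed data exactly the effect model used in the base case, so that a change can be attributed to the handling of missing data.
3. Add a delta-shift (tipping-point) table that lowers imputed scores in each arm separately, including the direction unfavourable to the non-inferiority claim, and report the shift at which non-inferiority is lost. Running both arms keeps the table valid whichever arm is finally tested.

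The cost is a wording change and a little extra analysis. Baseline scores are collected and surgery dates are needed to time follow-up, so no new data or patients are required. Investigators receive the randomisation key only after trial completion, so the rules can be fixed before then.
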